#### 3.6.2. Stool Samples

One day prior to their baseline and final study visits, participants collected stool samples using the OMNIgene GUT collection systems OMR205 and ME200. They kept the tubes at room temperature until delivery to the clinics the following day. The stool samples were vortexed, aliquoted into cryovials and stored at −80 °C until analysis.

DNA extraction from stool samples collected in OMR-205 was performed using the ZymoBIOMICS DNA/RNA Miniprep Kit (Zymo Research, Irvine, CA, USA) according to the manufacturer’s instructions. The quality and concentration of the extracted DNA were assessed on an Implen N60 NanoPhotometer (Implen GmbH, Munich, Germany) and visualized on a 1% agarose gel. Libraries for metagenomic sequencing will be prepared, and DNA will be sequenced by Annoroad Gene Technology Limited (Beijing, China).

The raw sequencing data will undergo quality check using FastQC (V0.11.9) [87] followed by preprocessing using Trimmomatic (V0.36) to remove adapter sequences, low-quality (Phred scores < 30), and short (<36 bp) sequencing reads [88]. Host contamination reads will be removed using “bbduk” from BBMap (V39.01) [89]. Read pairs will be joined using PEAR (V0.9.6) at the default setting [90] and any read pairs not joined by PEAR will be concatenated with a string of 50 N’s using the “fuse” function of the BBMAP package (V38.22-0) [89]. Joined and fused reads from different lanes of the same sample will be compiled into a final “clean” read sample file. HUMAnN (V3) will be used to identify and profile the functional potential of microbial communities in the samples [91]. Briefly, known microbial species will first be identified with MetaPhlAn2 [92]. A database of the samples will then be constructed by merging preconstructed, functionally annotated pangenomes through nucleotide mapping [93]. Finally, a translated search for reads not aligned to pangenomes will be performed using the UniRef90 database [94].

Metabolites from stool samples collected in ME-200 will be processed and analyzed as previously described [95].

### 3.7. Acute Sub-Study

During the baseline and final study visits, participants who consented to the sub-study consumed a bolus dose (500 mL) of their allocated milk. Sequential blood samples were drawn at 0, 60, 120, 180, 240, and 300 min to measure circulating levels of amino acids, insulin, and triglycerides.

Amino acid concentrations in plasma will be analyzed as described in Section 3.6.1. to assess the impacts of sustained milk consumption on circulating amino acid appearance. Circulating insulin and triglycerides will be assessed to determine the GlucoTRIG index of the study milks, a novel index for classifying the overall healthiness of meals based on the glycemic and lipemic responses they induce [56]. Insulin and triglycerides in plasma will be analyzed using Cobas e411 Analyzer (Roche, Basel, Switzerland) and Cobas c311 Analyzer (Roche, Basel, Switzerland), respectively, according to the manufacturer’s instructions. Briefly, the frozen plasma samples will be thawed, homogenized and centrifuged at 2000× *g* for 10 min before the sample is loaded into the analyzers with the appropriate reagent kits. Quality control for insulin will be performed using PreciControl Multimarker (Roche, Basel, Switzerland) and calibration carried out using Insulin CalSet (Roche, Basel, Switzerland) and pooled serum. Quality control for triglycerides will be performed using PreciControl ClinChem Multi 1 and 2 (Roche, Basel, Switzerland) and calibration carried out using Calibrator f.a.s. (Roche, Basel, Switzerland) and pooled serum.

During these timepoints, participants also completed a questionnaire to self-report appetite and satiety. This questionnaire, comprising eight 100 mm Visual Analog Scales, consists of questions relating to feelings of perceived hunger, satisfaction, fullness, and desire for specific food types [96]. This allows the study of potential adaptations to daily milk consumption.

### 4.2. Statistical Analysis

All data collected will be analyzed for both intention-to-treat (ITT) and per-protocol (PP) populations. The ITT population will include all randomized participants who have taken at least one serving of their assigned study milk whereas the PP population will include all randomized participants who have completed the study and have complied with at least 80% of the intervention without major protocol violations. All analyses will be undertaken using SPSS v28 (IBM, New York, NY, USA) or R version 4.3.3 (The R Foundation, Vienna, Austria) by blinded researchers with guidance from an independent biostatistician and statistical significance will be set at a two-tailed *p* value of less than 0.05.

All study outcomes will be summarized using descriptive statistics such as mean, standard deviation, median, range, frequency and percentage according to data type. Univariate and covariate analyses will be performed to evaluate and compare the changes for patient reported outcomes, blood biomarkers, blood pressure, anthropometric measurements, body composition, and functional tests. Chi square tests and logistic regression will be used to analyze categorical data. One-way ANOVA and general linear mixed models with ‘participant’ as a random factor, ‘study timepoint’ and ‘study allocation’ as fixed factors will be used to analyze continuous data. Further models incorporating baseline levels and other potential confounding or explanatory variables may also be used to explore the outcomes and the relationships between specific outcomes.

For stool microbiome analysis, the relative abundance of bacterial taxa, gene abundance, and alpha and beta-diversities will be compared. If these data do not meet the assumptions for parametric testing, the non-parametric permutation ANOVA known as ANCOMBC [99] will be used to analyze microbiome data to account for the high dimensionality, non-normality, and phylogenetic structure of the data.

A priori planned comparisons of within-group and between-group changes will focus on the changes from baseline to the week 12 endpoint.

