## 2. Materials and Methods

### 2.1. Study Design and Setting

The YUMMI study is a 12-week multi-arm, parallel, multi-center, single blinded randomized controlled trial carried out at the Dunedin and Christchurch campuses of the University of Otago, New Zealand. A total of 165 participants were randomized to one of four intervention groups: habitual diet supplemented with 500 mL of either bovine milk, caprine milk, or ovine milk daily for 12 weeks; or a habitual diet with no additional milk (control) group to study the effects of sustained consumption of these milks on digestive comfort, nutrient intake, and metabolism among older women. Bovine milk powder was supplied by Miraka Ltd. (Taupo, New Zealand), caprine milk powder by NIG Nutritionals Ltd. (Auckland, New Zealand), and ovine milk by Spring Sheep Milk Co. (Hamilton, New Zealand). After a lead-in period of 2 weeks, participants consumed their assigned milk, attended clinic visits for measurements and biological sample collection and completed validated questionnaires over the course of 12 weeks.

At baseline and after 12 weeks of the intervention, a subgroup of participants from each milk group consumed a bolus dose (500 mL) of their assigned milk, had sequential blood samples taken and completed assessments to assess acute postprandial plasma amino acids, triglycerides, insulin, and appetite hormones in response to consuming the study milks.

The trial protocol has been prospectively registered with the Australia and New Zealand clinical trials Registry (ANZCTR) with registration number ACTRN12622001161718. Data collection commenced in January 2023 and concluded on the 27th of March 2024 and lab analyses have commenced.

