### 2.4. Randomization and Blinding

Participants were randomly assigned to one of four groups: bovine milk, caprine milk, ovine milk, and control (no milk) in a 1:1:1:1 ratio with a pre-specified computer-generated random block randomization list prepared by the study statistician. Block sizes of eight were used without any stratification. To mimize bias, participant allocation was carried out by the principal investigator, who supplied the allocation for each participant to the research team a week before the participants were scheduled to come in for their baseline visits and all data analysis will be performed by blinded researchers.

Study participants were not informed about their milk intervention, but no attempt was made to mask the flavor of the milks. Researchers assessing study outcomes and conducting data analysis will remain blinded to participation allocation until the completion of statistical analyses for the primary and key secondary outcomes.

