### 2.5. Intervention

Participants in the milk groups were given a 4-week supply of their assigned milk powder at baseline (week 0), week 4 and week 8. They were asked to maintain their usual diet and consume one serving of their assigned milk twice daily, with breakfast and lunch, over the 12-week intervention period. Participants reconstituted their assigned milk powder by weighing out their daily portion (as detailed in Table 1) and dissolving it in lukewarm water before making up the milk to 500 mL and mixing it thoroughly. Once mixed, the milk was refrigerated. The following day, they would have half with breakfast and the other half with lunch. The daily portions were calculated to match the nutrient composition of fresh milk while providing the same volume of study milk to all participants in milk groups. Depending on the type of milk, the intervention would add 9–14 g of protein to each meal, totalling 18–29 g of protein each day. Participants were asked to consume their milk at breakfast and lunch to increase protein intakes during these meals, as protein intakes are typically low for these meals [60,61]. Participants in the control group were asked to follow their usual diet for 12 weeks with no restrictions on their milk or dairy intake.

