#### 3.2.2. Compliance Diary

After randomization, participants in the milk groups recorded their consumption of their assigned milk. This provides a comprehensive record of their compliance with study instructions and captures any changes that may have occurred throughout the study.

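### The ITT set requires having drunk the assigned study milk, a condition no control can meet and one that can exclude women from the milk arms only

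*Protocol article*

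**What the plan says.** Section 4.2 gives the rule for the main analysis set: "The ITT population will include all randomized participants who have taken at least one serving of their assigned study milk". Its scope is general: "All data collected will be analyzed for both intention-to-treat (ITT) and per-protocol (PP) populations". The PP set is limited to randomised women who finished the study and who "have complied with at least 80% of the intervention without major protocol violations".

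The comparator is described in three places. Section 2.1 lists, as one of the four randomised groups, "or a habitual diet with no additional milk (control) group". Section 2.4 allocates women to "bovine milk, caprine milk, ovine milk, and control (no milk) in a 1:1:1:1 ratio". Section 2.5 adds: "Participants in the control group were asked to follow their usual diet for 12 weeks with no restrictions on their milk or dairy intake".

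On the recording of intake, Section 3.2.2 says: "After randomization, participants in the milk groups recorded their consumption of their assigned milk". Section 2.6 likewise confines the compliance diary and the weighing of returned powder to the milk groups.

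Section 4.1 sizes the trial on each milk group against control: 34 women per group for a 0.6-point difference on the GSRS abdominal pain domain, raised to 40.

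**The concern.** Entry to the ITT set depends on an act that one randomised arm has no means of performing. Followed to the letter, the set has no comparator. If analysts keep the controls by their own decision, the milk arms pass through a filter applied after randomisation and the control arm does not. The groups compared are then no longer the groups as randomised, although the result would be reported as ITT.

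The PP rule raises a related question. Adherence to the intervention is measured only where there is milk to take, so the 80% threshold can select women only in the milk arms. Section 2.8 names gastrointestinal discomfort from added milk as a foreseeable event and the primary outcome is digestive comfort, so low intake could plausibly be related to the outcome.

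**Working it through.** **1. Who can satisfy the ITT rule.** The rule needs (a) randomisation and (b) one or more servings of the allocated milk. Milk-arm women can meet both. Controls meet (a), but under Sections 2.1, 2.4 and 2.5 they have no allocated milk, so (b) is impossible. Nothing in the article gives them another route into the set.

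**2. Size of the literal reading.**
- Inputs: 165 randomised, ratio 1:1:1:1, and "Block sizes of eight were used without any stratification".
- Average per arm: 165/4 = 41.25.
- Full blocks: 165 = 20 × 8 + 5. Twenty full blocks hold 20 × 2 = 40 controls, and the five remaining women include 0 to 2 more. The control arm therefore has 40 to 42 women if one list was used in sequence.
- Literal ITT set: 0 controls and at most 165 − 42 = 123 to 165 − 40 = 125 women. Every milk-versus-control contrast is undefined.

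**3. The plan's own sample size.**
- The standardised effect of 0.7 (stated for nutrient intake), two-sided 5% and 80% power give n = 2(1.960 + 0.842)²/0.7² = 32.04, so 33 per group. The t-test version gives 33.02, so 34. The stated 34 is reproduced.
- Attrition: 34/(1 − 0.15) = 40, as stated.
- The SD behind the GSRS calculation is not printed. Solving back from n = 34 and 80% power (t-test), the detectable standardised difference is 0.690, so SD = 0.6/0.690 = 0.87. This is inferred, not a stated input.

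**4. Can a milk-arm woman be randomised and never start?** Yes. Section 2.4 has the allocation released to the research team a week before the baseline visit, and Section 2.5 has powder first handed out at week 0. Under Section 2.3.3, women allocated to milk were invited to the sub-study before baseline, so some could have known by then that they were in a milk arm. A milk-arm woman who left in that interval would fail the rule. A control leaving at the same point would not, if controls are kept unconditionally.

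**5. Bias if controls are kept.** Let f be the fraction of a milk arm that never starts, and g the difference between those women's outcome and that of the rest, in SD units. The mean over all randomised women is (1 − f)m + f(m + g·SD) = m + f·g·SD, where m is the mean of those who remain. Dropping the non-starters therefore shifts the arm mean by f × g × SD. The values of f and g are assumptions, and SD = 0.87.

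| f | g = 0.5 | g = 1.0 |
|---|---|---|
| 2.5% | 0.011 (1.8% of 0.6) | 0.022 (3.6%) |
| 5% | 0.022 (3.6%) | 0.044 (7.3%) |
| 10% | 0.044 (7.3%) | 0.087 (14.5%) |

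For an arm of 41, f = 2.5% is about one woman and f = 10% about four. With f = 0 the bias is zero.

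**6. The PP rule, criterion by criterion.** Completion can be checked in every arm. So can the absence of major violations. Only the 80% criterion cannot. The diary and powder weights cover the milk groups only. The weekly milk food-frequency questionnaire records non-study milk, but the controls' intake was unrestricted, so no recorded intake could make a control non-adherent. The article gives no figure for completers who fall below 80%, so no bias can be calculated.

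**The case against.** The strongest reply is that nobody intends to discard the control arm. Section 2.1 makes it a randomised group, Section 4.1 powers the trial on it, and Section 4.2 puts study allocation in the model and plans between-group comparisons. The sentence was evidently written with the milk arms in mind. This is a fair reading. A reader might infer from the rule that controls will be dropped, and the rest of the article does not support that. What stands is that the rule as printed cannot be applied to a quarter of the women, and that the sensible repair leaves a one-sided filter.

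A reader might also infer that women who feel unwell on the milk are removed from ITT. They are not: one serving is enough, so a woman who starts, feels unwell and stops stays in. A woman who never starts cannot have reacted to the study milk, and Section 2.2 already excludes dairy intolerance and ruminant milk allergy.

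A third tempting step is to take the 15% predicted attrition as the share removed from a milk arm in PP, assume those women would score 1.0 point worse, and report a bias of 0.15 × 1.0 = 0.15 points, a quarter of the 0.6 MID. The article does not support this. The 15% inflates every group, control included, and the 1.0 point has no source. Nor is the PP control arm unselected, because completion and major violations apply to it as well.

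Finally, which set is primary and when the sets are fixed are details that an article commonly leaves to the SAP. Their absence here is not a fault.

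**Conclusion.** The ITT definition is wrong as stated. This is an error in the printed rule, so it is not a detail left for the SAP to supply, and it rests on no assumption. Taken literally, it loses about 41 of 165 women and with them the comparison the trial was sized for. Taken as probably intended, it describes a modified ITT under the name ITT.

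The demonstrated numerical effect is modest and uncertain. The range of 0.01 to 0.09 GSRS points (2% to 15% of the MID) depends on assumed non-starter rates of 2.5% to 10%, assumed differences of 0.5 to 1.0 SD and a back-solved SD. The true figure may be zero. In the PP set, the asymmetry is confined to the 80% adherence criterion and its size is unknown. The case for correction is that this rule governs every analysis and at present obliges the analyst to improvise for the control arm.

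**What to change.** - Define ITT as all 165 randomised women, analysed in the arm to which they were allocated, with no condition on intake.
- If a set requiring a first serving is still wanted, call it modified ITT or a sensitivity set and state explicitly how controls enter it.
- Treat milk-versus-control PP contrasts as supportive, and state that the 80% criterion selects women in the milk arms only.

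The cost is wording. No new data are needed, and any non-starters re-enter the analysis. Section 2.4 keeps analysts blinded until the primary and key secondary analyses are finished, so the change can be made without knowledge of the results while that holds. If all of roughly 41 women per arm contributed data, a milk-versus-control contrast would have about 87% power at the back-solved SD of 0.87, against 80% at 34 per arm.

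### The ITT set requires a serving of study milk, which no control woman can meet; waiving that for controls leaves an exposure-based set mislabelled as intention-to-treat

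*Protocol article*

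**What the plan says.** Section 4.2 applies two populations to everything measured: "All data collected will be analyzed for both intention-to-treat (ITT) and per-protocol (PP) populations". It then fixes the first of them: "The ITT population will include all randomized participants who have taken at least one serving of their assigned study milk".

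The four arms are "bovine milk, caprine milk, ovine milk, and control (no milk) in a 1:1:1:1 ratio" (section 2.4). Section 2.1 describes the fourth arm as "or a habitual diet with no additional milk (control) group", and section 2.5 adds: "Participants in the control group were asked to follow their usual diet for 12 weeks with no restrictions on their milk or dairy intake". The article gives no separate ITT rule for this arm.

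On timing, section 2.4 says the principal investigator "supplied the allocation for each participant to the research team a week before the participants were scheduled to come in for their baseline visits". Product is first handed out at week 0: "Participants in the milk groups were given a 4-week supply of their assigned milk powder at baseline (week 0), week 4 and week 8" (section 2.5). Records of intake exist for the milk arms only: "After randomization, participants in the milk groups recorded their consumption of their assigned milk" (section 3.2.2).

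**The concern.** An intention-to-treat set keeps every randomised participant in the arm allocated, so that randomisation protects the comparison. The rule here adds a condition on behaviour after randomisation, and that condition has meaning in only three of the four arms.

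The trial is sized for each milk group against control (section 4.1), which is the comparison across which the rule is uneven. The woman most clearly mishandled is one who is allocated milk, takes none of it, and still completes her weekly GSRS. Intention-to-treat exists to keep her, and this definition removes her. A control woman whose follow-up is identical stays in.

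The article states this rule itself, so it is not a detail left to a fuller protocol or an analysis plan.

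**Working it through.** **The plan's own figures.** Section 4.1 gives 34 women per group, raised to 40 for 15% attrition.
- For the stated effect size of 0.7, two-sided 5% and 80% power, the normal approximation 2 × ((1.960 + 0.842)/0.7)² gives 32.04, so 33. The two-sample t calculation gives 33.02, so 34.
- Attrition: 34/0.85 = 40.
- The GSRS calculation gives no SD and cannot be reproduced independently. With 34 per group and a difference of 0.6 it implies an SD of about 0.87.

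These figures are consistent, and the point does not depend on them.

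**Arm sizes.** 165/4 = 41.25 per arm. Blocks of eight give 20 full blocks (160 women, 40 per arm) plus 5 more women. If the list was used in order, control holds 40–42 women. The milk arms together hold about 165 × 3/4 = 123.75.

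**Literal reading.** Entry requires randomisation and at least one serving of the assigned milk. Controls have no assigned milk, so 0 of about 41 qualify. The set then holds at most 123–125 women, all in milk arms, and no milk-versus-control difference can be estimated.

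**Reading with controls exempt.** All of the roughly 41 controls stay, and each milk arm loses the women who took no serving. The number is not in the article, so the loss rate below is an assumption.

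| Assumed share with no serving | Lost per milk arm (of 41.25) | Lost over three milk arms (of 123.75) | Controls lost |
|---|---|---|---|
| 1% | 0.4 | 1.2 | 0 |
| 3% | 1.2 | 3.7 | 0 |
| 5% | 2.1 | 6.2 | 0 |

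Each planned comparison sets one milk arm against control, so the per-arm column is the relevant one.

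**What such a loss could do.** Suppose, purely as an illustration, that the excluded women's outcomes were observed and differed from the others' by 0.6–1.0 GSRS points in either direction. The shift in the milk-arm mean is the share dropped times that difference:
- 1 of 41 at 0.6 points: 0.015 points, about 2% of the 0.6 minimal important difference.
- 2 of 41 at 1.0 point: 0.049 points, about 8% of it.

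These are upper-end figures for that assumption, because women who leave the study early would mostly have no week-12 score.

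**Is there a window for it?** Allocation reaches the research team a week before baseline, and powder is first given at week 0. Outside the acute sub-study, section 2.5 has the mixed milk refrigerated and drunk the next day. A woman can therefore be randomised and never take a serving.

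**The case against.** The strongest reply is that this is loose wording with little practical effect. Most of that reply stands.

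- **No controls at all.** A reader might infer that the trial plans an analysis without a control arm. The documents do not support that: section 4.1 powers each milk group against control, and section 4.2 uses allocation as a fixed factor with planned between-group comparisons. The literal reading is a slip.
- **Size per comparison.** A reader might take the 4–6 women lost at an assumed 3–5% as the loss in every comparison. They are spread over three arms, so each comparison loses about 1.2–2.1. The only attrition figure given, 15%, is for the whole study and carries no timing.
- **Direction.** A reader might infer that the rule favours milk, by removing women who expect discomfort. Nothing in the article links leaving before a first serving to a worse GSRS change. Women who took no study milk have no symptoms from it, and women with dairy intolerance or milk allergy are excluded at entry (section 2.2).
- **Early leavers.** Planned comparisons focus on change from baseline to week 12. A woman who leaves before any serving would mostly have no week-12 score under either definition. A control woman without follow-up also contributes no change score.
- **The window.** Allocation went to the research team, not to participants, and Table A2 places allocation at week 0. Against that, section 2.3.3 says milk-group women were invited to the sub-study before baseline, so some could have inferred that they would receive milk.
- **Main analysis set.** Section 4.2 names neither population as the main one.
- **Milk against milk.** Those comparisons apply the same rule on both sides, so this asymmetry does not touch them.

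None of this repairs the definition. It still has no stated meaning for one arm, and under the charitable reading it is not intention-to-treat.

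**Conclusion.** The definition is wrong as written. Read literally it admits no control woman, which is surely unintended. With controls exempted, it selects on a post-randomisation act in three arms only, and the label ITT misdescribes it. Confidence in this is high, because it rests on the text alone.

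The consequence for the results is uncertain and may be small or nil. At an assumed 1–5% with no serving, each milk-versus-control comparison would lose about 0.4–2.1 of about 41 milk-arm women and no controls. The rule matters mainly for women who take no milk yet keep supplying data, and the article does not count them. The documents do not support a claim of material bias or of bias in favour of milk. This should be fixed, but it does not by itself put the trial's conclusions in doubt.

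**What to change.** Replace the ITT sentence in section 4.2 with a definition that takes in all 165 randomised women, analysed in the arm allocated, whether or not any study milk was taken. State that this set is used for the primary and key secondary between-group comparisons.

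If a set of women who took at least one serving is wanted, give it another name, such as exposed milk-arm participants, and do not use it for comparison with control.

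The cost is one or two sentences and no new data; any women excluded for taking no serving return to the denominator. Section 2.4 keeps analysts blinded until the primary and key secondary analyses are complete, so the change can be made and dated before they see allocation. It does not settle how absent week-12 scores are handled, which is a separate matter.

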The primary aim of the study is to determine the effects of 12-week ruminant milk consumption on digestive comfort of older women using the Gastrointestinal Syndrome Rating Scale (GSRS). The key secondary aim is to determine the effects of 12-week ruminant milk consumption on nutrient intake of older women based on biomarkers of nutrient status (amino acids and trace elements concentrations) and self-reported dietary data (protein intake). Exploratory outcomes include evaluating the effects of 12-week ruminant milk consumption on bowel habits (bowel movement diary), cardiometabolic health (blood lipids, hemoglobin A1c (HbA1c), body weight, body composition, blood pressure), physical function (timed walk test, handgrip strength test), physical activity (accelerometry), and sleep (accelerometry and Leeds Sleep Evaluation Questionnaire), mood (Patient-Reported Outcomes Measurement Information System (PROMIS): Anxiety, Depression), sensory and emotional responses (sensory and emotional assessments), and the composition and predictive function of the gut microbiota (metagenomic sequencing of stool samples).

In addition to the 12-week intervention described above, we also incorporated an investigation to determine the acute effects of consuming a bolus dose of ruminant milk on digestive comfort (appetite and satiety questionnaire), digestive function (amino acid appearance), and acute cardiometabolic effects (GlucoTRIG index [56]). This investigation was conducted both at baseline and again after the 12-week intervention in a sub-group of participants to study potential adaptations to nutrient metabolism with regular milk intake.

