## 3. Study Outcomes and Measurements

### 3.1. Weekly Questionnaires

Participants completed weekly questionnaires on the study app or on paper from baseline until the end of the 12-week intervention period. These weekly questionnaires are described briefly below.

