#### 3.1.1. Gastrointestinal Syndrome Rating Scale (GSRS)

The primary outcomes are between-group differences in abdominal pain scores and bowel comfort scores from baseline to week 12, measured using the abdominal pain domain in the GSRS. Upon enrolment, participants filled out the GSRS on a weekly basis. The GSRS is a validated questionnaire that uses a 7-level Likert scale (1–7) to assess the frequency and intensity of gastrointestinal symptoms experienced in the past 7 days [63]. It contains 15 items divided into five domains covering the gastrointestinal system: Reflux, Abdominal pain, Indigestion, Diarrhea, and Constipation. A higher score represents more frequent and/or severe symptoms experienced by the patients. Significant responders to the intervention will be those reporting at least a 0.6 reduction in abdominal pain severity score, the minimal important difference [64], compared to baseline.

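### Weekly GSRS scores are collected, but the only pre-specified contrast, change from baseline to week 12, has no power for discomfort that appears when milk is started and then fades

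*Protocol article*

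**What the plan says.** All references are to the protocol article.

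- **Aim (Section 1).** "The primary aim of the study is to determine the effects of 12-week ruminant milk consumption on digestive comfort of older women".
- **Collection (Section 3.1.1).** "Upon enrolment, participants filled out the GSRS on a weekly basis". Each score covers the previous seven days. Table A2 marks the GSRS in the lead-in (weeks -2 to -1), at week 0 and at week 12, with a footnote that it is weekly. The general sentence in Section 3.1 has the weekly questionnaires starting at baseline.
- **Primary outcome (Section 3.1.1).** "The primary outcomes are between-group differences in abdominal pain scores and bowel comfort scores from baseline to week 12". Responders are those with "at least a 0.6 reduction in abdominal pain severity score", so the responder rule counts improvement only.
- **Sample size (Section 4.1).** 34 women per group for a difference of 0.6 in the abdominal pain domain from baseline to week 12, each milk group against control, with 5% alpha and 80% power; raised to 40 per group.
- **Analysis (Section 4.2).** "A priori planned comparisons of within-group and between-group changes will focus on the changes from baseline to the week 12 endpoint". Continuous data go to one-way ANOVA and to mixed models with participant as a random factor, where "study timepoint’ and ‘study allocation’ as fixed factors will be used to analyze continuous data". The timepoints are not listed and no timepoint-by-allocation term is named.

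**The concern.** Section 6 presents digestive discomfort as a major barrier to drinking milk. Discomfort in the first weeks after adding 500 mL a day bears directly on that barrier. The week-12 score describes only the seven days before the final visit, after some eleven weeks of use.

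If one milk caused symptoms early on and was then tolerated, the contrast fixed in advance would have an expected value of zero. The responder rule would not register the worsening either. Any early-weeks comparison made later would be post hoc, although the scores for it are already in hand. A null result at week 12 could then be read as a statement about digestive comfort over the whole 12 weeks, which that contrast cannot support.

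**Working it through.** **1. The plan's own figures.** No SD is printed, so the 34 cannot be reproduced directly. It can be inverted. With n = 2·SD²·(1.960 + 0.842)²/0.6² = 34, SD = 0.6·√17/2.802 = 0.883 (0.870 by the t-test formula). The attrition step reproduces: 34/(1 - 0.15) = 40.

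**2. Power of each contrast.** Inputs from the article: difference 0.6, n = 34 per group, two-sided 5%. Assumptions: SD of a weekly change 0.883; equal correlation ρ between weekly changes of 0.3, 0.5 or 0.7.

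For the mean of m weekly changes, SE = 0.883·√[(2/34)·(1 + (m - 1)ρ)/m]. For one week this is 0.214, and 0.6/0.214 = 2.80, which gives the planned 80%. For weeks 1-4 at ρ = 0.5, SE = 0.214·√0.625 = 0.169 and 0.6/0.169 = 3.54, which gives 94%.

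| True effect | Week 12 | Mean weeks 1-4 | Mean weeks 1-12 |
|---|---|---|---|
| 0.6 in weeks 1-2 only | difference 0; 5% | 0.30; 36-53% | 0.10; 9-12% |
| 0.6 in weeks 1-4 only | difference 0; 5% | 0.60; 89-98% | 0.20; 20-35% |
| 0.6 throughout | 0.60; 80% | 0.60; 89-98% | 0.60; 91-100% |

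Ranges run from ρ = 0.7 to ρ = 0.3. The 5% is the type I error rate. The 12-week mean is a poor detector of a transient effect because it dilutes it.

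A slower fade gives the same picture. If the difference is 0.6·(12 - k)/11 in week k, it is 0.00 at week 12, 0.30 averaged over weeks 1-12, and 0.6·9.5/11 = 0.52 averaged over weeks 1-4.

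**3. The mixed model without an interaction.** Suppose weeks 0 to 12 all enter with main effects only and complete data. The allocation term then estimates one constant difference over 13 timepoints. A 0.6 rise in weeks 1-4 appears as 4·0.6/13 = 0.18, and the model has no term that places it early.

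**4. Baseline.** Let raw weekly scores have variance σ² and equal correlation r.

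- Single baseline score: Var(week 12 - baseline) = 2(1 - r)σ².
- Mean of three pre-milk scores (weeks -2, -1, 0): σ²[1 + (1 + 2r)/3 - 2r] = (4/3)(1 - r)σ².
- SD ratio: √[(4/3)/2] = √(2/3) = 0.82 at any r.
- If only two pre-milk scores exist, the variance is 1.5(1 - r)σ² and the ratio is √0.75 = 0.87.

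Under this structure with a single baseline, the correlation between two weekly changes is (1 - r)/[2(1 - r)] = 0.5, the middle value used in step 2.

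**The case against.** The strongest reply is that week 12 is a coherent choice. The stated research gap is long-term consumption, the aim concerns 12 weeks of milk, and the primary outcome, sample size and planned comparison all use the same contrast. Early tolerability is a different question. A condensed article may also leave supportive longitudinal analyses to a statistical analysis plan that is not shown. This stands: nothing is contradictory, and the primary endpoint need not change.

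Some stronger readings are tempting but unsupported:

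- **That only two timepoints are used and early discomfort would be missed.** Section 4.2 says the comparisons focus on week 12. It also says all data collected will be analysed, calls for descriptive summaries of all outcomes, and lists a mixed model that could take in the weekly scores. Adverse events and a daily bowel diary are recorded too. An early rise could therefore surface, but not as a planned test.
- **That the protocol expects symptoms to adapt.** "This allows the study of potential adaptations to daily milk consumption" refers to the appetite and satiety scales of the acute sub-study, and the Introduction speaks there of nutrient metabolism. Neither predicts that GSRS scores rise and fall.
- **That baseline is undefined.** Section 3.5 and Table A2 place it at week 0. Averaging the pre-milk scores is a gain in precision, not the repair of an error.
- **That averaging 12 scores cuts the SD to between 0.60 and 0.85.** That is √[(1 + 11r)/12] for raw scores at r = 0.3 to 0.7. For change from a single baseline the ratio is √[(13/12)/2] = √(13/24) = 0.74 at any r.
- **That three non-significant contrasts would establish no effect.** Failure to reject does not show absence of effect, however many contrasts are tested.

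**Conclusion.** The point holds as a limit on what the planned comparison can show. It is neither a contradiction nor a numerical error. The one pre-specified contrast detects a sustained 0.6 difference with the planned 80% power and a fully transient one at the 5% error rate only. The mixed model, as described, does not clearly close that gap.

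The power figures rest on an SD inferred from the sample size, on assumed equal correlations, and on invented early-effect profiles. The article gives no evidence on whether such an effect exists, and women with dairy intolerance or milk allergy are excluded. A cheap clarification is worth making; the sample size and the week-12 primary stay as they are.

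**What to change.** In Section 4.2, or in the statistical analysis plan if one exists, before unblinding:

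1. Keep the week-12 change in GSRS abdominal pain as primary. Estimate it from one longitudinal model of all weekly scores, listing the timepoints and including a timepoint-by-allocation term.
2. Use the mean of the lead-in and week-0 scores as baseline.
3. Name the between-group difference in the mean over weeks 1-4 as a supportive contrast. The mean over weeks 1-12 is optional.
4. Report these beside the week-12 result, and word any null result at week 12 as applying to symptoms at week 12, not to digestive comfort over the whole 12 weeks.

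The cost is a few sentences and modest extra analysis, with no new data. With three milk-control comparisons, one or two further contrasts each means three to six more estimates. They should be labelled supportive and not used for the primary claim. Data collection ended in March 2024, but Section 2.4 keeps analysts blinded until the primary and key secondary analyses are complete. The change can be made as pre-specification only if that point has not been passed.
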